### Intervention

#### Probiotic and placebo

The main intervention in this trial is a dietary food supplement powder containing seven probiotic bacterial strains: lactobacillus salivarius W57, lactobacillus casei W56, lactobacillus rhamnosus W71, lactococcus lactis W58, enterococcus faecium W54, lactobacillus plantarum W62 and lactobacillus acidophilus W22 (manufactured by Winclove Probiotics B.V., Netherlands; marketed as OMNi-BiOTiC® metabolic by Institut AllergoSan GmbH, Graz, Austria) In addition, the probiotic contains 2000 IU cholecalciferol. Other ingredients are corn starch, maltodextrin, fructo-oligosaccharides, galacto-oligosaccharides, polydextrose, plant proteins, potassium chloride, magnesium sulfate, manganese sulfate and lactose. By comparison, the placebo is very similar to the probiotic visually and in taste and smell. Its ingredients are corn starch, maltodextrin, potassium chloride, magnesium sulfate and manganese sulfate. Both Verum and Placebo are packaged in blank sachets, so that patients, caregivers, investigators and outcome assessors are blinded to their content.

On each sachet, the expiration date and the study acronym (ProPCO-RCT) is clearly shown. 50 sachets are packed in one box, where the instruction for ingestion, the expiration date, the randomization code and the ingredients are noted. The bacterial strains are mentioned on every box with the symbol +/- (regardless if the strains are included or not). Every participant receives 4 boxes, in total 200 sachets. An excess number of sachets (the intervention period is only 180 days) is included in case the participant loses a few.

#### Metformin

The metformin drug used in this trial is Glucophage, a commercially available extended release metformin-hydrochloride pill, owned by Merck GmbH, Vienna, Austria. It is packaged in boxes containing 200 pills with no special markings regarding the trial.

#### Blinding

The blinding is applied to the trial participants and the investigators, who serve as both care providers and outcome assessors.

A treatment code table was generated via Winclove Probiotics B.V., Netherlands. Each Verum/Placebo box containing 50 sachets receives a unique code, corresponding to the treatment code table. The blinding of the sachet boxes is also done at Winclove Probiotics B.V., Amsterdam, Netherlands.

To ensure proper stratification of the 20 individuals taking probiotics/placebos who also have two endoscopies during the trial, the randomisation is separated into two lists: The first list contains the 100 individuals without endoscopies, and the second list consists of the 20 participants that are assigned to the endoscopic procedures. The investigators have both lists available and assign participants the corresponding code in ascending order.

Since we are only randomizing dietary supplements and placebos in a blinded manner in healthy participants, we do not expect any complications from the trial participation that would require emergency unblinding. However, in case of a medical emergency involving a participant of the trial, study investigators may be reached through the Endocrinology Ward, Division of Endocrinology and Diabetology, Medical University of Graz on a 24/7 basis.

The randomization can be unblinded at the Endocrinology ward, where 120 sealed envelopes contain the allocation of each number. Only the envelope containing the treatment number for the patient in question may be opened. Both the principal investigator and the sponsor have to be notified as soon as possible of the emergency unblinding.

#### Concomitant therapies

Apart from the metformin and the probiotic formula as well as the placebo, no additional medicinal products will be administered by the investigators as part of this study. However, a subgroup of PCOS patients has additional diagnoses and therefore we need to account for any medications the participants might have to take. If a participant takes any non-permissible concomitant therapy (for example antibiotic treatment), this has to be documented in the CRF at the next visit. Thyroid hormone derivatives, renin-angiotensin-aldosterone system inhibitors (such as angiotensin-converting enzyme inhibitors, angiotensin I and II inhibitors), as well as topical or locally applied ointments, drops, creams, salves, gels and powders (provided their ingredients do not have a systemic effect) may be taken during the trial without further need for documentation.

In contrast, antibiotic treatments, metformin and other antidiabetic drugs, antacid medication (proton pump inhibitors), steroid hormone treatments as well as probiotic products (not including probiotics contained in food products such as yoghurt) should not be taken during the trial as well as prior to the trial based on the exclusion criteria. Should a situation require a trial participant to take any of these substances (such as an antibiotic due to infection), the circumstances and duration of the drug intake should be documented in the CRF at the next visit.

### Outcome parameters

#### Primary outcome

The primary endpoint of the study is a change in serum free testosterone concentration in women with PCOS after a 6-month intervention with probiotics compared to placebo treatment.

PCOS combines several different phenotypes and symptoms which may vary greatly, however free testosterone is one of the most consistent biomarkers of PCOS and its symptoms and therefore the most suited for designation as the primary outcome measure and may provide the most benefit if successfully lowered due to the intervention [30].

#### Secondary outcomes

Glucose metabolism via HOMA and Matsuda indices as determined through an oral glucose tolerance test.Other hormonal parameters of PCOS (Anti-Müllerian hormone; androstenedione; follicle-stimulating hormone FSH; luteinizing hormone LH; dehydroepiandrosterone-sulphate DHEA-S; 17α-hydroxy-progesterone; 17β-hydroxy-estradiole; total testosterone, 25-hydroxy-cholecalciferol).Hirsutism (modified Ferriman-Gallwey score).Body weight (body-mass-index BMI; waist-to-hip-ratio).Gut permeability and inflammation (functional sucrose-lactulose-mannitol test; surrogate parameters: serum diaminooxydase; stool zonulin; calprotectin; lipopolysaccharide; soluble cluster of differentiation sCD14; bacterial DNA).Gut lumen and mucosa microbiome composition (16 S-RNA gene sequencing).Phytoestrogen production -log10 (equol to daidzein concentration ratio in urine) obtained via the soy challenge test)Quality of life (PCOS questionnaire; depression questionnaires; diet questionnaires).

#### Exploratory outcome measures

Lipid metabolism (low-density lipoprotein LDL; high-density lipoprotein HDL; lipoprotein a LP(a); triacylglycerol;)FACS analysis (B cell subtypes).Metabolomics of stool and blood.Gene expression analysis in blood and biopsy samples.Changes in incretin levels.

### Statistical considerations

This study is conducted to compare two treatment groups with each other in respect to PCOS parameters. In the double-blind part, comparisons between the probiotic and the placebo arms will be performed to show that probiotics are superior to placebos. The comparison of the open-label metformin arm with the probiotic arm will be exploratory.

#### Sample size calculation

Prior to this RCT, we conducted a short pilot trial with 30 women with PCOS (EC number 30–205 ex 17/18), randomly assigning 10 women into three probiotic intervention arms respectively, both to test our methodology as well as to assess the feasibility of improving PCOS symptoms with probiotics ([name], [name], [name], [name], 2020, data on file).

In the pilot study 10 participants received OMNi-BiOTiC® metabolic for 3 months and showed a median (minimum-maximum) reduction in free testosterone levels of -0.3 pg/ml (-1.7-2.5). We assumed that over 6 months the reduction in the probiotic group would be improved to -0.6 pg/ml, which corresponds to 20% of the free testosterone levels found in healthy women based on the cut-off value of 3,16 pg/ml free testosterone in our Endocrinology Lab platform. A sample size of 54 in each group would have 80% power to detect a difference in means of -0.6 pg/ml assuming that the common standard deviation was 1.1 pg/ml using a two group t-test with a 5% two-sided significance level. Including a 10% dropout, 60 participants per group had to be included. For the metformin group in the open part of the trial, 60 participants were recruited as well. Therefore, the total anticipated sample size was 180.

#### Statistical analysis of outcomes

The analysis of the collected data in the study will be performed with SAS v9.4. The primary analysis will be performed on the intention-to-treat population. Details regarding the defined populations and the statistical analysis will be provided in the statistical analysis plan (SAP). The SAP will be prepared before unblinding the trial.

The analyses described below will be performed for the comparison of the probiotic and the placebo arms and the probiotic and the metformin arms, separately.

Demographic and baseline characteristics will be summarized and compared between the groups descriptively. The data will be presented as summary tables and, where appropriate, as plots. Continuous variables will be presented as means, standard deviation, median, minimum and maximum, for categorical data frequencies and relative frequencies will be used.

The primary outcome, changes in serum free testosterone concentration from baseline (screening visit) to 6 months (visit 2) will be compared between the probiotic and the placebo arms by analysis of covariance (ANCOVA) with serum free testosterone concentration at month 6 as dependent variable, and the baseline serum free testosterone concentration and treatment group as covariates. If the assumptions of the ANCOVA are not fulfilled, the changes in serum free testosterone concentration (i.e. difference visit 2 - baseline) will be compared between the groups by t-test or Mann-Whitney-U-test. A two-sided p-value of < 0.05 is considered to indicate statistical significance.

For the secondary and exploratory endpoints, group comparisons will be performed using parametric or nonparametric methods for unpaired data (as appropriate). I.e. the continuous secondary endpoints will be analysed similarly to the primary endpoint. In addition, linear mixed models will be used to analyse the group difference over the three time points (baseline, visit 2 and follow-up visit).

The collected stool samples will be sequenced with Illumina and the raw data will be uploaded on the Galaxy server of the Medical University of Graz. Microbiome analysis will be conducted using the QIIME 2 pipeline of the Galaxy server, the samples will be compared in respect to alpha- and beta-diversity using established methods. The results can be downloaded directly from the server.

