## Methods and analysis

### Study design

This phase IV trial is monocentric, randomized and double-blinded with one additional open-label treatment arm serving as the positive control. Two randomizations are performed. In the first randomization, participants are randomized in a 2:1 ratio to either the double-blind part or open-label metformin part. This open randomization is performed via the web-based randomization service “Randomizer” (Randomizer; Institute for Medical Informatics, Statistics and Documentation, Medical University of Graz, Austria; available at: www.randomizer.at, accessed: September 3, 2021).

The patients who are randomized to the double-blind part are further randomized in a 1:1 ratio to either the probiotic group or the placebo group. The second randomization as well as the allocation concealment is performed by Winclove Probiotics B.V, Netherlands. To ensure that the 30 participants undergoing endoscopic procedures are balanced over the three groups, both randomizations are stratified for endoscopy (yes/no). Both randomizations are performed at visit 1.The study takes place at Graz University Hospital, Department of Internal Medicine, Division of Endocrinology and Diabetology, Endocrinology Outpatient Clinic.

The treatment arms are the following:

Probiotic (number n = 60).Probiotic placebo (n = 60).Open-label metformin (500 mg twice daily, n = 60).

The framework of the study is to show that the effects of the probiotic intervention are superior to the placebo arm. The metformin arm serves as a standard benchmark treatment arm and positive control. The study design is outlined in Fig. 1. This study protocol adheres to the SPIRIT recommendations.

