In addition, two gastro-/sigmoidoscopies each will be performed at the beginning and the end of the intervention period in 30 voluntary participants (10 from each treatment arm planned) in order to obtain biopsy samples from the stomach, duodenum and sigmoid colon. These samples are used for the assessment of the mucosal gut microbiome as opposed to the luminal gut microbiome composition in stool samples. An overview of the timeline and visit schedule is provided in Table 1.

**Table 1 Tab1:** Overview of number of visits and outcome assessments

Visits	Screening visit	Endoscopy 1	Visit 1	Endoscopy 2	Visit 2 End of Intervention	Voluntary follow-up
Weeks +/- 3 or more days	(-4)-(-1) (+/-3 days)	-1 (+/-3 days)	0 (+/-3 days)	24–26 (+/-3 days)	26 (+/-3 days)	52 (+/-3 days)

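### The primary ANCOVA and its fallback test leave out endoscopy, the factor by which both randomisations are stratified; the effect is small and conservative

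*Protocol article*

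**What the plan says.** On the design, the protocol's Study design section states that "both randomizations are stratified for endoscopy (yes/no", and gives the purpose: "To ensure that the 30 participants undergoing endoscopic procedures are balanced over the three groups". The Blinding section shows how this works in the double-blind part: "the randomisation is separated into two lists". It continues: "The first list contains the 100 individuals without endoscopies, and the second list consists of the 20 participants that are assigned to the endoscopic procedures". According to the Timeline section, endoscopy is planned in "30 voluntary participants (10 from each treatment arm planned", which is one sixth of each arm of 60.

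On the analysis, the section Statistical analysis of outcomes specifies "analysis of covariance (ANCOVA) with serum free testosterone concentration at month 6 as dependent variable". Its remaining terms are fixed in the same sentence by the words "and the baseline serum free testosterone concentration and treatment group as covariates". Should the ANCOVA assumptions fail, the changes from baseline "will be compared between the groups by t-test or Mann-Whitney-U-test". Neither analysis contains endoscopy, and no section gives a reason for leaving it out. Continuous secondary endpoints are to be handled in a similar way to the primary one. The analyses are run for probiotic against placebo and, separately, for probiotic against metformin. Further details are deferred to an SAP, to be prepared before unblinding.

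**The concern.** The usual principle is that a factor which restricts the randomisation also enters the analysis. Stratified allocation removes most of the chance imbalance in that factor between the arms, so the treatment estimate varies less than it would under simple randomisation. A model without the factor does not take credit for this. If the factor is related to the outcome, its variance stays in the error term and the standard error is overstated.

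What is at stake is a little power and a test that runs slightly below its nominal level. The plan has little power to give away, because it is sized for 80%. The protocol writes out the model terms and the fallback, so the omission is a stated rule and not a detail left open.

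**Working it through.** **Inputs from the protocol.** The section Sample size calculation gives a difference of 0.6 pg/ml, SD 1.1 pg/ml, two-sided 5%, a two-group t-test, 54 evaluable per group and 10% dropout. The Timeline section gives 10 endoscopy participants per arm of 60. The endoscopy share is p = 10/60 = 1/6, or 9 of 54 evaluable if dropout is even, so p(1 − p) = 5/36 = 0.139.

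**Input that must be assumed.** The documents give no difference in outcome between endoscopy volunteers and other participants. It is written as g, in units of the within-stratum SD, and varied over 0, 0.25, 0.5 and 1.0.

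**Step 1: the plan's own figure.** The normal approximation n = 2(1.96 + 0.8416)² × 1.1² / 0.6² = 52.8 gives 53 per group. With the noncentral t distribution, power is 0.794 at 53 and 0.802 at 54. So 54 is reproduced, and 54/0.9 = 60 per group.

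**Step 2: what the omission does to the standard error.** With the stratum balanced between arms, the estimate is the same with or without the term. Only the estimated error variance changes. It grows by the factor 1 + 0.139 g², and the standard error by the square root of that:

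- g = 0.25: √1.0087 = 1.004
- g = 0.5: √1.0347 = 1.017
- g = 1.0: √1.139 = 1.067

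**Step 3: simulation.** There were 40,000 runs per setting, with 54 per arm, 9 per arm in the endoscopy stratum and within-stratum SD 1.1. The treatment test was run without and with an endoscopy term. The baseline covariate was left out of both models.

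| Assumed g | Type I error without / with term | Power without / with term | Power loss (points) |
|---|---|---|---|
| 0 | 0.0480 / 0.0478 | 0.8048 / 0.8045 | 0.0 |
| 0.25 | 0.0471 / 0.0478 | 0.8022 / 0.8045 | 0.2 |
| 0.5 | 0.0444 / 0.0478 | 0.7951 / 0.8045 | 0.9 |
| 1.0 | 0.0355 / 0.0478 | 0.7658 / 0.8045 | 3.9 |

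The simulation error is about √(0.05 × 0.95/40,000) = 0.001 for the type I error and √(0.8 × 0.2/40,000) = 0.002 for power. A value of 0.048 is therefore compatible with 0.05.

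**Step 4: check by hand.** The standardised effect is 0.6/(1.1 × √(2/54)) = 2.834, and the critical value on 106 degrees of freedom is 1.983. Leaving the term out multiplies the critical value by the factor from Step 2. Approximate power is then:

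- g = 0: Φ(2.834 − 1.983) = 0.803
- g = 0.5: Φ(2.834 − 1.983 × 1.017) = 0.793
- g = 1.0: Φ(2.834 − 1.983 × 1.067) = 0.764

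The losses of about 1 and 4 points agree with the simulation.

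**Step 5: the other convention.** Suppose instead that 1.1 is the SD before the stratum is removed. The term then gains power over 80.2%. If the stratum explains 1%, 2% or 5% of the residual variance (assumed), power at 54 per group becomes 80.6%, 81.0% or 82.2%. By R² = 0.139 g²/(1 + 0.139 g²), these shares correspond to g of about 0.27, 0.38 and 0.62. Direction and order of size are the same as in Step 3.

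**The case against.** The strongest objection is that almost nothing follows. The stratum was created to spread the biopsy subset evenly over the arms, and the protocol does not present endoscopy as a predictor of free testosterone. The primary model already adjusts for baseline free testosterone, so only a stratum difference that remains after that adjustment would matter. The calculations above leave the baseline out and therefore do not measure the effect in the planned ANCOVA exactly. All of this stands, and it is why the severity is low.

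It may also be said that the unseen SAP could add the term. It could. But the protocol names the covariates and the fallback, so an SAP that follows this text would carry the omission forward.

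Two stronger readings are tempting, and the documents support neither.

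- A reader might infer that an analysis which departs from the design is invalid. It is not: the estimate is unbiased and the type I error stays at or below its nominal level.
- A reader might infer that the loss is larger for microbiome and gut-permeability endpoints, as the endpoints closest to the endoscopy substudy. The protocol sends microbiome data through a QIIME 2 pipeline with unspecified established methods, and does not clearly apply this ANCOVA to them. All participants do the permeability test at home, so that test is no reason for the stratum. Mucosal endpoints exist only inside the endoscopy stratum, where the factor is constant. No figure in the documents points to a larger effect.

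**Conclusion.** The point holds at low severity. Both randomisations are stratified by endoscopy, and neither the primary ANCOVA as written nor its fallback uses that factor.

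The consequence is at most a slightly conservative test. Power falls by about 0 to 1 point for assumed stratum effects up to 0.5 SD and by about 4 points at 1.0 SD. The type I error is then 0.044 and 0.036 respectively.

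These sizes rest on an assumed stratum effect, on 9 endoscopy participants among 54 evaluable in each arm, and on a model without the baseline covariate. If endoscopy is unrelated to the outcome, nothing is lost by leaving it out, and practically nothing by putting it in.

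**What to change.** Before unblinding, in the SAP and in the protocol text:

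- Add endoscopy (yes/no) as a fixed factor to the primary ANCOVA.
- Add it likewise to the ANCOVA-type models for continuous secondary endpoints measured in all participants.
- Stratify the fallback by endoscopy: a linear model of the change with treatment and stratum in place of the t-test, or the van Elteren test in place of Mann-Whitney U.
- Leave the factor out for endpoints measured only in the endoscopy subset.

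If the sponsor prefers to omit the factor, one sentence giving the reason should be written before unblinding, because a term added later would look data-driven. The cost is one model term and one degree of freedom out of more than 100. The sample size of 54 evaluable and 60 randomised per arm does not change.

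### If the ANCOVA assumptions fail, the primary comparison falls back to change-score tests without baseline as a covariate; one baseline-adjusted analysis that tolerates skew would be better

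*Protocol article*

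**What the plan says.** In the protocol article, the section Statistical analysis of outcomes sets the primary comparison of probiotic and placebo as an ANCOVA, with month-6 free testosterone as the response and baseline value and treatment group as covariates. It continues: "If the assumptions of the ANCOVA are not fulfilled, the changes in serum free testosterone concentration" (visit 2 minus baseline) "will be compared between the groups by t-test or Mann-Whitney-U-test". The threshold is conventional: "A two-sided p-value of < 0.05 is considered to indicate statistical significance". Continuous secondary endpoints are to be handled in a similar way. Further detail is left to a SAP that is to be written while the trial is still blinded.

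The section Sample size calculation works on a difference in means: "A sample size of 54 in each group would have 80% power to detect a difference in means of -0.6 pg/ml". The SD is set at 1.1, the same in both arms, and the test behind the figure is given as "using a two group t-test with a 5% two-sided significance level". The section then adds dropout: "Including a 10% dropout, 60 participants per group had to be included".

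**The concern.** The fallback is stated in the article, so it is a rule and not a detail left open. It has three weaknesses.

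- **The t-test on change is a partial remedy.** In its standard form it needs normality and equal variance, as ANCOVA does. It relaxes only the linear baseline relation and the equal slopes, by fixing the baseline coefficient at 1.
- **Mann-Whitney on change has a different target.** It compares ranks of change, whereas the trial is sized on a mean difference in pg/ml. Which of the two the primary result addresses would be settled by how the outcome data look.
- **Covariate adjustment is lost in both.** Adjusted alternatives that cope with skew exist, such as ANCOVA on logs or on ranks.

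At stake is power for the primary endpoint, and a primary result whose meaning is not fixed in advance.

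**Working it through.** **1. The plan's own figure.** Inputs from Sample size calculation: difference 0.6, SD 1.1, two-sided 5%, 80% power. Allocation is 1:1 (Study design: "further randomized in a 1:1 ratio to either the probiotic group or the placebo group"). The noncentrality at 54 per arm is 0.6 / (1.1 × √(2/54)) = 2.83 on 106 degrees of freedom, which gives 80.2% power. The exact requirement is 53.74, so 54, and 54 / 0.9 = 60. The stated 54 and 60 are reproduced.

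**2. Cost of dropping the covariate.** Let rho be the baseline-to-month-6 correlation (not in the article; assumed 0.3 to 0.8), with equal variance σ² at both visits.
- Var(change) = 2σ²(1 − rho)
- ANCOVA residual variance = σ²(1 − rho²)
- Ratio = 2/(1 + rho)

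The article does not say whether 1.1 is the SD of change or of level. If it is the SD of change, the ANCOVA SD is 1.1 × √((1 + rho)/2):

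| rho | variance ratio | t-test on change, power at 54 | ANCOVA, power at 54 | ANCOVA n per arm for 80% |
|---|---|---|---|---|
| 0.3 | 1.54 | 80.2% | 93.6% | 36 |
| 0.5 | 1.33 | 80.2% | 90.0% | 41 |
| 0.7 | 1.18 | 80.2% | 86.1% | 46 |
| 0.8 | 1.11 | 80.2% | 84.1% | 49 |

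A ratio of 1.33 equals losing 1 − 1/1.33 = 25% of the sample.

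**3. Skewed data, proportional effect.** Simulation with 4,000 trials per setting, 54 per arm, lognormal values with mean 3 pg/ml and CV 0.5 (both assumed), and a 20% reduction (0.6/3). Power:

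| rho | log ANCOVA | rank ANCOVA | untransformed ANCOVA | Mann-Whitney on change | t-test on change |
|---|---|---|---|---|---|
| 0.3 | 72.5% | 70.1% | 67.2% | 46.5% | 44.8% |
| 0.5 | 80.2% | 77.8% | 74.8% | 59.7% | 57.0% |
| 0.7 | 92.5% | 90.3% | 88.0% | 80.6% | 77.1% |
| 0.8 | 98.0% | 96.4% | 95.9% | 92.6% | 90.4% |

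Log ANCOVA minus Mann-Whitney is 26.0, 20.5, 11.9 and 5.4 points. Log ANCOVA minus the t-test is 27.7, 23.2, 15.4 and 7.6 points.

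**4. Skewed data, constant shift of 0.6 pg/ml.** Same layout:

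| rho | rank ANCOVA | untransformed ANCOVA | Mann-Whitney on change | t-test on change |
|---|---|---|---|---|
| 0.3 | 74.2% | 58.5% | 48.9% | 42.1% |
| 0.5 | 80.8% | 65.8% | 63.8% | 53.8% |
| 0.7 | 92.2% | 80.5% | 83.5% | 73.8% |
| 0.8 | 97.5% | 91.3% | 94.8% | 87.9% |

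Both fallback tests are below rank ANCOVA throughout. Mann-Whitney passes untransformed ANCOVA at rho 0.7 and 0.8.

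**5. Type I error.** With a fixed rule (a normality check on the ANCOVA residuals, then the change-score fallback) it was 4.8% to 5.2% across all normal and lognormal null settings.

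**The case against.** Several points on the other side are sound.

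- **Free choice among three tests.** A reader might infer that the analyst may pick among ANCOVA, t-test and Mann-Whitney after seeing results. Taking the smallest of the three p-values would raise type I error to 7.5% to 8.7% in these simulations. The article does not plan that. It sets an order, and the SAP can fix both the trigger and the choice between the two fallback tests before unblinding. Their absence from the article is no finding.
- **Always weaker under skew.** A reader might also infer that the fallback is worse than the planned ANCOVA whenever data are skewed. It is worse for a proportional effect. For a constant shift, which is closer to how the trial was sized, it can match or exceed untransformed ANCOVA at high correlation.
- **Baseline is not discarded.** A change score subtracts it with coefficient 1. What is lost is the regression adjustment.
- **The t-test can be a remedy** if the failure lies in linearity or equal slopes.
- **Planned power may be intact.** The sizing uses a two-group t-test. If 1.1 is the SD of change and the data are roughly normal, the t-test fallback still has 80.2%, and the gain from ANCOVA is a bonus.
- **The pilot is weak evidence of skew.** A median of -0.3 with range -1.7 to 2.5 puts the extremes 1.4 below and 2.8 above. In normal samples of 10, extremes at least that lopsided occur 25% of the time (12.5% in this direction).

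These points limit the claim but do not rescue the fallback: in the skewed settings simulated, an adjusted analysis suited to skew did better than either change-score test.

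**Conclusion.** The concern holds as one of efficiency and of a shifting target. The article fixes change-score tests without covariate adjustment as the primary fallback. One of them leaves the distributional problem unsolved, and the other leaves the mean difference behind. The variance penalty is 11% to 54% for rho 0.8 down to 0.3. Under lognormal data with a 20% reduction, the power loss against log ANCOVA is about 5 to 26 points for Mann-Whitney and 8 to 28 for the t-test. No inflation of type I error is claimed.

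The result rests on an assumed correlation, an assumed lognormal shape with CV 0.5, and equal variances at both visits for the ratio. The SD of change in the lognormal runs ranged from 0.98 to 1.78 and not the planned 1.1, so the comparison between methods carries the argument and the absolute powers are illustrative. Whether the fallback would be needed at all cannot be judged from the article.

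**What to change.** Before unblinding, name one baseline-adjusted primary analysis in the protocol and SAP:

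- ANCOVA of log free testosterone at visit 2 on log baseline and arm, reported as a ratio of geometric means; or
- to keep the difference in pg/ml, untransformed ANCOVA with heteroscedasticity-robust standard errors.

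Make the t-test and Mann-Whitney test on change sensitivity analyses. If a rank test is wanted, use rank ANCOVA. Apply the same to the continuous secondary endpoints, which follow the primary method.

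The cost is a change of wording. The log option gives up a pg/ml difference for a ratio. The robust option keeps the scale and deals with unequal variance, but it uses the same estimate as untransformed ANCOVA, so it should not be expected to recover the power that log or rank ANCOVA gains under skew.
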